### Statistical considerations

#### Trial sample size

This study is designed to test if the analgesic efficiency of Kypho-IORT is superior to standard-of-care EBRT in patients with painful vertebral metastases by comparing percentages of patients with a pain reduction of at least 3 points on VAS at defined points in time (day 1, week 2 and 6 after start of treatment).

Assuming a pain reduction of VAS-3 points at day one (first day after Kypho-IORT, one day after the first EBRT) for 40% of the patients after Kypho-IORT vs 5% of the patients after EBRT under standard pain medication (no change of the pretherapeutic pain medication 12 h after Kypho-IORT or 24 h after the first EBRT), the study will require 22 patients in each arm in order to have a two-sided alpha of 0.05 and a power of 0.817. Including a dropout rate of 20% at least 54 patients have to be recruited. The effect size was estimated on the basis of the results of the preceded phase I/II trial [11] and the results of RTOG 9714 [3].

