**Methods:**

This phase III study includes patients ≥50 years of age with up to 4 vertebral metastases and a pain score of at least 3/10 points on the visual/numeric analogy scale (VAS). Patients randomized into the experimental arm (A) will undergo Kypho-IORT (Kyphoplasty plus IORT with 8 Gy prescribed to 13 mm depth). Patients randomized into the control arm (B) will receive EBRT with either 30 Gy in 10 fractions or 8 Gy as a single dose. The primary end point is pain reduction defined as at least − 3 points on the VAS compared to baseline at day 1. Assuming that 40% of patients in the Kypho-IORT arm and 5% of patients in the control arm will achieve this reduction and 20% will drop out, a total of 54 patients will have to be included to reach a power of 0.817 with a two-sided alpha of 0.05. Secondary endpoints are evaluation of the percentage of patients with a pain reduction of at least 3 points at 2 and 6 weeks, local tumor control, frequency of re-intervention, secondary fractures/sintering, complication rates, skin toxicity/wound healing, progression-free survival (PFS), overall survival (OS) and quality of life.

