### Objective and primary endpoint

The primary objective of this study is to test if the analgesic efficiency of Kypho-IORT is superior to standard-of-care EBRT in patients with painful vertebral metastases. The primary end point is to evaluate the percentages of patients with a pain reduction of at least 3 points (VAS) at the first post-interventional day (i.e. one day after Kypho-IORT in Arm A and one day after the begin of fractionated or single-shot EBRT in Arm B).

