#### Inclusion criteria

Age ≥ 50 yearsKarnofsky Performance Index ≥60initial pain score (VAS) of at least 3 under standard pain medication (change of the pain medication will me monitored)documented history of cancer (i.e. histological confirmation of the primary tumor)painful osteolytic metastases involving a maximum of 4 vertebrae of the thoracic/lumbar spine, which are accessible for Kypho-IORTwritten informed consent

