### Arm a: Kypho-IORT

Kypho-IORT will be carried out under general anaesthesia as extensively described before [8–11]. All patients will be placed in prone position on a radiolucent table. An intraoperative low-energy x-ray device (Intrabeam®, Carl Zeiss Meditec AG, Oberkochen, Germany) will be used for intraoperative radiotherapy, the centre of the metastasis shall be chosen for the isocenter of the radiation.

The cement augmentation can be performed either as kyphoplasty or in a vertebroplasty technique. Each patient must receive early post-operative imaging of the treated vertebra to assess any leakage of cement. The direction of leakage and the clinical symptoms associated (symptomatic vs. asymptomatic) must be documented at this stage.

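### The primary responder definition has no analgesic condition, but the rates behind the sample size assume unchanged pain medication over an unclear window that differs by arm

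*Protocol article*

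**What the plan says.** The section Objective and primary endpoint compares the "percentages of patients with a pain reduction of at least 3 points (VAS) at the first post-interventional day". The Methods part of the abstract does the same ("The primary end point is pain reduction defined as at least" 3 points below baseline at day 1). Neither mentions analgesics.

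The section Trial sample size states its response rates conditionally: "for 40% of the patients after Kypho-IORT vs 5% of the patients after EBRT under standard pain medication". It explains standard pain medication as "no change of the pretherapeutic pain medication 12 h after Kypho-IORT or 24 h after the first EBRT". On those rates, "the study will require 22 patients in each arm" "in order to have a two-sided alpha of 0.05 and a power of 0.817".

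Elsewhere medication is only observed. The inclusion criteria say that "change of the pain medication will me monitored" (typographical slip in the source), and the Pain section under Assessment of efficacy parameters records current medication alongside each VAS. Data analysis plans an intention-to-treat comparison by chi-square or Fisher's exact test and does not use medication to classify patients. On Arm A, the article says that "Kypho-IORT will be carried out under general anaesthesia as extensively described before". It describes no anaesthesia for Arm B.

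**The concern.** A 3-point fall with unchanged medication is a narrower event than any 3-point fall. The article defines success as the wider event and takes its planning rates from the narrower one. A patient whose VAS falls because analgesics were added on the day of treatment is a responder under the endpoint section but falls outside the condition in the sample size section. The article does not say which prevails.

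This matters because the stated objective is the analgesic efficacy of Kypho-IORT itself. The outcome is self-reported, no blinding is described, the two treatments are plainly distinguishable to the patient, and the reading is taken one day after an operation in one arm only. If added analgesia is more common in Arm A, the resulting error favours the trial's hypothesis.

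**Working it through.** **Step 1. The plan's own figure.** Inputs from Trial sample size: rates 0.40 and 0.05, n = 22 per arm, two-sided alpha 0.05. With mean rate p̄ = (0.40 + 0.05)/2 = 0.225 and the normal approximation with pooled variance under the null:

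power = Φ{ [ (pA − pB)·√n − 1.96·√(2·p̄·(1 − p̄)) ] / √( pA(1 − pA) + pB(1 − pB) ) }

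= Φ{ [0.35 × 4.690 − 1.96 × 0.5906] / 0.5362 } = Φ(0.903) = 0.817.

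The stated power reproduces. The arithmetic is not in dispute; the question is which event the 40% and 5% describe.

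**Step 2. The texts side by side.**

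| Place | Event | Medication condition |
|---|---|---|
| Abstract, Methods | VAS fall ≥ 3 at day 1 | none |
| Objective and primary endpoint | VAS fall ≥ 3 at day 1 | none |
| Trial sample size | VAS fall of 3 at day 1 | unchanged; 12 h in Arm A, 24 h in Arm B |
| Inclusion criteria; Pain | – | monitored or recorded only |
| Data analysis | – | none |

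**Step 3. The window.** It can be read in two ways.

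- *Medication unchanged during the first 12 h or 24 h.* An increase between 12 h and 24 h breaks the condition in Arm B but not in Arm A.
- *Back on pre-treatment medication by 12 h or 24 h.* Early analgesia is excused in both arms, but for longer in Arm B. An increase still running between 12 h and 24 h then breaks the condition in Arm A but not in Arm B.

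The two readings tilt in opposite directions. On neither is the condition the same in both arms.

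**Step 4. What an analgesic artefact could do under the endpoint as written.** Assumptions: 22 per arm, true response 5% in both arms, no artefact in Arm B, and analgesia lifting apparent Arm A response to q. The documents supply no value for q, so a range is shown. The probability of a significant result is the sum, over all pairs (i, j) with p ≤ 0.05, of Bin(i; 22, q) × Bin(j; 22, 0.05).

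| q | Chi-square (uncorrected) | Fisher |
|---|---|---|
| 5% (no artefact) | 1.5% | 0.3% |
| 10% | 6% | 2% |
| 15% | 18% | 9% |
| 20% | 33% | 20% |
| 30% | 64% | 51% |

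If Arm B is lifted too, the effect shrinks. At 20% against 15% the probabilities are 7% and 4%.

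**Step 5. What the stricter definition could cost.** Suppose the 40% described any fall, and a share s of those Arm A responders had increased analgesics and were rescored. The Arm A rate becomes 0.40 × (1 − s). By the formula in step 1, with 5% in Arm B:

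- s = 0.1: rate 36%, power 0.737
- s = 0.2: rate 32%, power 0.644
- s = 0.3: rate 28%, power 0.540

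The shares s are also assumptions.

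**The case against.** The best defence is that the article means one endpoint throughout. The inclusion criteria take the baseline score under standard pain medication, the sample size section uses the same phrase for day 1, and medication is recorded with every VAS. On that view both readings are meant to be taken under standard medication, and the scoring of patients whose medication changes is detail for the full protocol or analysis plan. That is a plausible account of the intention. It does not remove the conflict, because the two places that define the endpoint omit the condition and the place that states it gives arm-specific windows of unclear meaning.

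Several stronger readings are tempting, and the objection to each of them stands.

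- A reader might infer that analgesia can create responders only in Arm A. An ordinary analgesic increase does so in Arm B as well. Only perioperative analgesia is specific to Arm A, and its use is inferred: the article states general anaesthesia and describes no perioperative analgesics.
- A reader might infer that the 12 h and 24 h windows favour Arm A. That holds on one reading and reverses on the other.
- A reader might infer that a positive result could not be attributed to Kypho-IORT at all. The Background reports a reduction of at least 3 points persisting beyond the first postoperative day in 79.1% in the phase I/II trial, and response is compared again at weeks 2 and 6. Neither settles day 1, but both speak against so absolute a conclusion.

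It is also fair that the artefact rates are hypothetical and drive the result, and that an equal look-back reaching into the operation could turn postoperative analgesia into non-response and bias against Arm A. The fix has to allow for that.

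**Conclusion.** The inconsistency is in the text shown and concerns the primary endpoint. The trial is sized on response with unchanged medication, while the endpoint as defined counts any 3-point fall. Following the endpoint section literally, analgesic-driven falls count as success in either arm, probably more often in Arm A, and confidence in attributing a positive day-1 result to Kypho-IORT is weakened to that extent.

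The size cannot be fixed from the documents. It runs from minor (6% by chi-square, 2% by Fisher, if apparent Arm A response rises only to 10%) to serious (64% and 51% at 30%), assuming no true effect and no artefact in Arm B. The existence of two definitions is certain. The direction and extent of any bias are inference, and the stated power of 0.817 is correct for the rates given.

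**What to change.** Reconcile the abstract, Objective and primary endpoint, and Trial sample size into one responder definition:

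- Response is a VAS at least 3 points below baseline at day 1, and a patient whose analgesics are above the pre-treatment level at that reading is scored as a non-responder. This carries the medication condition into the endpoint. It narrows no change to no increase, and that choice should be stated.
- State what 12 h and 24 h mean, and replace them for scoring with one reference period of the same length immediately before the day-1 VAS in both arms, chosen so that it does not include the operation itself.
- Report the version that ignores medication as a sensitivity analysis.

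This governs scoring only and leaves untouched what analgesia patients may receive.

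The cost is mainly wording, plus data collection: the Pain section records current medication, and the rule needs intake recorded for the whole reference period. The Arm A response rate may be lower, and power with it (about 0.64 if the rate is 32% rather than 40%). The 40% and 5% should therefore be confirmed as rates for the reconciled definition before analysis.

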#### Data analysis

Data will be analysed on an intention to treat basis. All variables will be described by descriptive statistics (frequencies, means and standard deviation, medians and minimum, maximum, depending on data distribution). The Chi-square test or Fisher’s exact test will be used for categorical data. For continuous data, parametric or non-parametric mean comparison tests will be used. The Kaplan-Meier method with log-rank tests will be used to estimate relapse-free survival and overall survival.

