### Screening and randomization

After informed consent, all patients will be screened for inclusion and exclusion criteria and obtain a patient ID. A baseline visit will then be performed, which includes the assessment of the KPS and VAS scores, comorbidities and medication, a gross neurological exam, the documentation of the underlying primary cancer and the completion of the QoL questionnaires to obtain baselines. If not performed before, a CT or MRI scan of the spine will have to be performed. After fulfilment of all inclusion criteria and in the absence of exclusion criteria, patients will then be allocated into any of the two arms by block randomization (block sizes of 2 or 4 and stratification by institute). Patients randomized into Arm A will undergo Kypho-IORT, patients randomized into Arm B will undergo standard EBRT (10 × 3 Gy or 1 × 8 Gy).

The intervention (Arm A or B) should begin within a time frame of 14 days after randomization.

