### Arm B: external beam radiotherapy

Patients randomized into arm B will receive conventional external beam radiotherapy, either as fractionated radiotherapy with 30 Gy delivered in 10 fractions of 3 Gy or as single-dose irradiation with 8 Gy. Each center must select and adhere to one treatment option (fractionated or singe-dose irradiation). Radiotherapy can be given as per established local standards (3D-conformal radiotherapy or intensity-modulated radiotherapy, local standards for target volume and risk organ delineation, local dose constraints). Patients will need to be seen at least once weekly by physicians and evaluated for adverse reactions.

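### Randomisation is stratified by institute and baseline scores are collected, but the named tests use neither: a small efficiency loss on the primary endpoint, a clearer one on quality-of-life scores

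*Protocol article*

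**What the plan says.** All references are to the protocol article.

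- **Screening and randomization:** allocation is by "block randomization (block sizes of 2 or 4 and stratification by institute". The baseline visit records VAS and the QoL questionnaires.
- **Arm B: external beam radiotherapy:** "Each center must select and adhere to one treatment option", so within the control arm the EBRT schedule is a property of the institute.
- **Objective and primary endpoint:** the endpoint is the "percentages of patients with a pain reduction of at least 3 points (VAS) at the first post-interventional day". The Secondary endpoints section uses the same responder definition at weeks 2 and 6 and lists QLQ-C30 and BM22.
- **Trial sample size:** the assumption is "40% of the patients after Kypho-IORT vs 5% of the patients after EBRT under standard pain medication", giving "22 patients in each arm in order to have a two-sided alpha of 0.05 and a power of 0.817".
- **Data analysis:** "The Chi-square test or Fisher’s exact test will be used for categorical data", and "For continuous data, parametric or non-parametric mean comparison tests will be used". No stratum and no baseline covariate is named, and neither is ruled out.

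**The concern.** Blocking within institute removes between-institute variation from the arm comparison by design. A test that ignores the strata still counts that variation as noise, so it becomes conservative when institutes differ in response. Here they could differ both in local practice and in the EBRT schedule each has fixed. In the same way, comparing QoL scores between arms without the recorded baseline leaves explainable variance in the error term and leaves chance baseline imbalance uncorrected. In a trial of 54 patients, free precision is worth having. At stake is precision and the agreement of the analysis with the design, not the validity of the result.

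**Working it through.** **1. Reproduce the stated power.** Inputs from Trial sample size: p1 = 0.40, p2 = 0.05, n = 22 per arm, two-sided alpha 0.05. The mean proportion is 0.225. With the pooled-variance normal approximation and no continuity correction:

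z = [0.35 × √22 − 1.960 × √(2 × 0.225 × 0.775)] / √(0.40 × 0.60 + 0.05 × 0.95) = (1.642 − 1.157) / 0.536 = 0.903, so power = Φ(0.903) = 0.817.

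This matches the article. The design was therefore sized for an unstratified comparison of two proportions.

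**2. Exact power of the two named tests, no strata, 22 per arm.** Full enumeration of the two binomials gives 0.860 for uncorrected chi-square and 0.773 for Fisher. With a common response rate of 22.5% in both arms, the type I errors are 0.051 and 0.024. The gap of 0.860 − 0.773 = 8.7 points exists before any institute effect enters.

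**3. Effect of stratifying the primary test.** The article gives neither the number of centres nor the between-centre variation, so both are assumed. Simulation: 44 patients, blocks of 2 or 4 within institute, a normal institute effect on the logit scale, and overall rates held at 40% and 5%. There were 8,000 runs for power, and 4,000 under the null with 22.5% in both arms. CMH is without continuity correction.

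| Centres | Centre SD | CMH power | Chi-square power | Difference (points) | Fisher power | Null: chi-square | Null: CMH |
|---|---|---|---|---|---|---|---|
| 3 | 0 | 0.857 | 0.862 | −0.5 | 0.795 | 0.049 | 0.048 |
| 3 | 0.5 | 0.856 | 0.856 | 0.0 | 0.793 | 0.045 | 0.051 |
| 3 | 1.0 | 0.848 | 0.836 | +1.2 | 0.767 | 0.040 | 0.050 |
| 5 | 0 | 0.849 | 0.861 | −1.2 | 0.797 | 0.051 | 0.049 |
| 5 | 0.5 | 0.854 | 0.858 | −0.4 | 0.798 | 0.043 | 0.046 |
| 5 | 1.0 | 0.866 | 0.856 | +1.0 | 0.793 | 0.037 | 0.045 |
| 8 | 0 | 0.836 | 0.855 | −1.9 | 0.793 | 0.051 | 0.048 |
| 8 | 0.5 | 0.843 | 0.855 | −1.2 | 0.794 | 0.050 | 0.050 |
| 8 | 1.0 | 0.864 | 0.863 | +0.1 | 0.801 | 0.037 | 0.043 |

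The Monte Carlo standard error of one power figure is about √(0.86 × 0.14 / 8000) = 0.004.

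Balanced layouts were also simulated with 20,000 runs each: 2, 4, 7 or 11 centres with 11, 6, 3 or 2 patients per arm in each. CMH minus chi-square was −1.2 to +0.1 points at SD 0, +0.2 to +1.0 at SD 0.7, and +1.0 to +2.8 at SD 1.2. At SD 1.2 the type I error of chi-square was about 0.033 to 0.038.

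**4. Split the gap to Fisher.** Take 3 centres at SD 1.0. CMH minus Fisher is 0.848 − 0.767 = 8.1 points. Of this, 0.848 − 0.836 = 1.2 points come from stratifying, and 0.836 − 0.767 = 6.9 points come from Fisher's own conservatism. The continuity-corrected CMH has power 0.687 to 0.731 across the table's settings, below Fisher in each. The correction therefore matters more than the stratification.

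**5. Baseline adjustment of continuous scores.** With equal variances at baseline and follow-up and correlation ρ (assumed, not in the article), the variance under ANCOVA is:

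- relative to follow-up scores: 1 − ρ²;
- relative to change scores: (1 − ρ²) / [2(1 − ρ)] = (1 + ρ)/2.

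An illustrative unadjusted power of 0.80 becomes Φ[(1.960 + 0.842)/√ratio − 1.960].

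| ρ | Ratio vs follow-up | Power | Ratio vs change | Power |
|---|---|---|---|---|
| 0.3 | 0.91 | 0.84 | 0.65 | 0.94 |
| 0.5 | 0.75 | 0.90 | 0.75 | 0.90 |
| 0.7 | 0.51 | 0.98 | 0.85 | 0.86 |

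**The case against.** The case on the other side is strong in four respects.

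- **Level of detail.** The article's analysis section is a short list of test families. It does not exclude strata or covariates, and an analysis plan that is not shown may set them. This stands as a reason not to call anything here an error. It does not remove the point, because the tests that the section does name are the unstratified and unadjusted forms, and better ones are available from data already collected.
- **Validity.** Unadjusted tests remain valid after stratified randomisation, are simple, and agree with the sample size calculation. One EBRT schedule per centre does not bias an arm comparison that is blocked within centre. All of this stands.
- **Size on the primary endpoint.** A reader might infer that ignoring institute costs 12 to 16 points of power, since CMH beats Fisher by that much in some settings with SD 1.2. The figures do not support that. In one such setting (7 centres, 3 per arm each, overall rates not held at 40% and 5%), power is 0.809 for CMH, 0.779 for chi-square and 0.648 for Fisher. Only 3.0 of the 16.1 points come from stratifying.
- **Baseline VAS.** A reader might also infer that chance imbalance in baseline pain goes uncorrected in the pain endpoints. Every listed VAS endpoint is a responder rate defined by change from baseline, so it already uses the baseline score. The argument for adjustment reaches the QoL scores, and VAS only if it is also analysed as a continuous score.

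**Conclusion.** The point holds as an efficiency recommendation. The named tests are valid but leave out the randomisation stratum and the collected baselines.

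On the primary endpoint, institute-stratified CMH is worth about −1 to +3 points of power against uncorrected chi-square, and down to about −2 where eight centres do not differ. The benefit appears only when institutes differ, and then mainly as a type I error closer to 0.05. These figures rest on assumed numbers of centres and centre SDs. Fisher's exact power of 0.773, below the stated 0.817, is mainly a matter of which listed test is chosen. That choice is a live one: the expected number of responders per arm, averaged over the arms, is 22 × 0.225 = 4.95, just under the usual rule-of-thumb threshold of 5, and the article states no switching rule.

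For QoL scores, and any continuous VAS analysis, the loss is clearer: 9%, 25% or 49% of variance against follow-up scores at an assumed ρ of 0.3, 0.5 or 0.7. This concerns secondary outcomes, and the article does not say whether follow-up or change scores would be compared.

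**What to change.** In the Data analysis section:

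1. Name as the primary analysis the CMH test without continuity correction, stratified by institute, and report a stratified risk difference with 95% CI. Pool very small institutes only with others that use the same EBRT schedule, by a rule fixed in advance.
2. Analyse QLQ-C30/BM22, and any continuous VAS score, by ANCOVA or a repeated-measures model with the baseline score as covariate and institute as factor.
3. Keep the unadjusted tests as sensitivity analyses.

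The cost is wording only, since institute and the baseline scores are already recorded. The one downside is a possible loss of about 1 to 2 points of power on the primary endpoint if institutes do not differ. A side benefit is that a single prespecified test replaces the open choice between chi-square and Fisher.

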#### Ethics and informed consent

The trial will be carried out in compliance with the protocol, the principles laid down in the declaration of Helsinki, version as of October 1996 (as long as local laws do not require to follow other versions), in accordance with the ICH Harmonised Tripartite Guideline for Good Clinical Practice (GCP), the harmonized standards for Medical Devices (ISO 14155) and all other applicable regulatory requirements (local, regional and global). Standard medical care (prophylactic, diagnostic and therapeutic procedures) remains in the responsibility of the treating physician of the patient. This study was approved by the local ethics committee (Medical Ethics Commission II of the Faculty of Medicine Mannheim, University of Heidelberg, 2013-593 N-MA) and the Federal Office of Radiation Protection (Z5–22462/2–2013-116). All patients participating in the study need to provide written informed consent at least 24 h prior to the intervention.

